## Abstract

**Background:**

A cancer diagnosis elicits greater distress than any other medical diagnosis, and yet very few studies have evaluated the efficacy of structured online self-help therapeutic programs to alleviate this distress. This study aims to assess the efficacy over time of an internet Cognitive Behaviour Therapy (iCBT) intervention (‘*Finding My Way*’) in improving distress, coping and quality of life for individuals with a recent diagnosis of early stage cancer of any type.

**Methods/Design:**

The study is a multi-site Randomised Controlled Trial (RCT) seeking to enrol 188 participants who will be randomised to either the *Finding My Way* Intervention or an attention-control condition. Both conditions are delivered online; with 6 modules released once per week, and an additional booster module released one month after program-completion. Participants complete online questionnaires on 4 occasions: at baseline (immediately prior to accessing the modules); post-treatment (immediately after program-completion); then three and six months later. Primary outcomes are general distress and cancer-specific distress, with secondary outcomes including Health-Related Quality of Life (HRQoL), coping, health service utilisation, intervention adherence, and user satisfaction. A range of baseline measures will be assessed as potential moderators of outcomes. Eligible participants are individuals recently diagnosed with any type of cancer, being treated with curative intent, aged over 18 years with sufficient English language literacy, internet access and an active email account and phone number. Participants are blinded to treatment group allocation. Randomisation is computer generated and stratified by gender.

**Discussion:**

Compared to the few prior published studies, *Finding My Way* will be the first adequately powered trial to offer an iCBT intervention to curatively treated patients of heterogeneous cancer types in the immediate post-diagnosis/treatment period. If found efficacious, *Finding My Way* will assist with overcoming common barriers to face-to-face therapy in a cost-effective and accessible way, thus helping to reduce distress after cancer diagnosis and consequently decrease the cancer burden for individuals and the health system.

**Trial registration:**

Australian New Zealand Clinical Trials Registry ACTRN12613000001796 16.10.13

## Background

Despite improvements in treatment and survival rates, a cancer diagnosis continues to elicit greater distress than any other medical diagnosis [1]. Research has consistently found that 30 to 40 per cent of recently diagnosed patients experience clinically significant depressive or anxiety disorders [2,3]. Distress is most acute during the first 12 months after diagnosis, when a range of medical treatments take place, following which the prevalence reduces to levels comparable with the community [4]. Consequently, distress management within the first 12 months after diagnosis has been recognised as an integral component of a patient’s clinical treatment [5,6]. Despite this, distress and psychiatric disorders among cancer patients often go under-recognised and untreated [7]. This particularly applies to the 30% of Australian cancer patients who reside in rural or regional areas, where access to specialist cancer services is limited [6].

### Psychological approaches that alleviate distress

Over the past two decades, a range of psychological interventions to alleviate distress have been empirically investigated, predominantly among women with breast cancer. Intervention research has focused on developing and evaluating interventions that target the known psychological predictors of maladjustment [8], namely, low social support, prior anxiety and depression (vulnerability to distress), and maladaptive coping, particularly repression of emotions, helplessness/hopelessness, and cognitive and behavioural avoidance. Interventions tested have included those based on Cognitive Behavioural Therapy (CBT) [9], Supportive Expressive Therapy (SET) [10], psycho-educational programs [11], mindfulness-based therapy [12], and peer-support groups [13]. There is clear meta-analytic evidence that all of these conventional psychosocial interventions are efficacious compared to control groups in facilitating adjustment [14]; with large effect sizes (ES) found for depression (ES = 1.2), anxiety (ES = 1.99), and functional adjustment / quality of life (QOL) (ES = 0.91) [14]. However, CBT has the largest evidence base for treating cancer-related distress to date [14], with most studies suggesting that treatment for distress at the time of cancer diagnosis is more effective than after cancer treatment has been completed [11].

### Need for novel approaches to improve access

While demonstrably efficacious, there several barriers to attending face-to-face therapy in the Australian setting. First, there are limited psychosocial services freely available in the public health setting, with the current capacity not sufficient to meet the demand [6]. This is particularly evident in rural and remote areas where access to multidisciplinary cancer care is problematic, and resulting inequities in health outcomes are well recognised [6]. Second, even when psychosocial services are offered in urban settings, research suggests that less than 25% of Australians attend [15], with low attendance attributed to a variety of barriers including: personal barriers, such as ongoing stigma associated with seeking mental health assistance [16,17], and illness-related barriers such as patients’ reduced physical capacity for additional appointments [17]. As a result of these barriers, national government supportive care policies have recognised that innovative methods of increasing access to supportive care throughout the treatment trajectory are required for all cancer patients [6].

One such innovative method of increasing patient access to supportive care is through internet-based provision of psychosocial services [16-18]. Since 2000 a plethora of randomised controlled trials and systematic reviews have examined internet-based interventions for both psychological [19,20] and physical [17,18] health complaints. Of these interventions, self-guided web-based interventions offer the particular advantage of overcoming the majority of the barriers discussed above for both rural and urban patients, along with anonymity, privacy and convenience of progressing through a program at the user’s own pace. Such interventions tend to be highly structured into modules, are derived from theory (predominantly cognitive behaviour therapy), and have been adapted from existing evidence-based print-resources or face-to-face therapy [21]. Consistent with research on face-to-face therapy, internet Cognitive Behaviour Therapy (iCBT) interventions have the largest evidence base for efficacy in improving both mental health conditions [22] and, increasingly, coping with chronic physical health conditions [17,18].

### Status of iCBT for cancer distress

Given that cancer consumers prefer multi-media to print resources [23], and that 84% of Australians have access to the internet [24], web-based interventions, and in particular iCBT-based interventions, appear a logical format for the wide dissemination of psychological treatment for cancer patients. However, the evidence-base for self-guided iCBT-based psychological therapy in cancer is only now emerging [25-28].

Two groups [26,28] developed and evaluated structured self-guided online CBT-based coping programs for women with recently diagnosed early-stage breast cancer. Similar in design, their programs were both multi-component, and contained 6–10 self-guided CBT-based modules, biomedical information, links to other cancer resources and websites, and asynchronous discussion boards. Both studies showed evidence for the efficacy of their respective interventions: The smaller of the two studies [28] found one significant interaction where women with poorer baseline perceived health status experienced greater improvements in perceived health over time when assigned to the intervention, despite a small sample and consequent lack of power. The larger study [26] found the intervention was efficacious in improving self-efficacy for coping with cancer, regulating negative mood, and reducing cancer-related post-traumatic symptoms. However, as each of these studies involved only breast cancer patients, efficacy could not be demonstrated across cancer types.

In the third study, Duffecy et al. [27] ran a small RCT of 31 post-treatment survivors of various cancer types to examine the feasibility and acceptability of an 8-week Internet Support Group (ISG) combined with an Individual Internet Intervention (III), compared with the III alone. The study supported feasibility and acceptability of the combined program, and found that both conditions produced large reductions in depressive symptoms in participants with high baseline distress. However, the study was underpowered to detect improvement over time and time x treatment effects; further, it examined efficacy in post-treatment survivors, rather than patients currently undergoing treatment. Current CBT literature suggests that a more effective time to implement such interventions may be in the immediate post-diagnosis period, when patients are likely to be experiencing higher levels of distress generally [4].

Our research group was the first to pilot test a 6-week iCBT program for people with any type of early stage/curatively treated cancer, and designed to be delivered soon after diagnosis [25]. In contrast to the previous three programs which all depended on group-support as a key feature, our study tested an individual self-guided web-based intervention for newly diagnosed patients that was independent of moderators and peer-support components, and was therefore consistent with the large evidence base for CBT [14]. Program content was derived from our evidence-based print self-help breast cancer workbook [29], but heavily revised and expanded to ensure relevance to heterogeneous cancer populations. In a case-series design, participants (n = 12) were assessed at baseline and after completing the program. Analysis found the intervention led to reductions with moderate associated effect sizes in negative affect, helplessness/hopelessness, anxious preoccupation, and fatalism. Results therefore provided preliminary support for the potential efficacy of the web-based CBT program for improving cancer-related distress and anxious preoccupation after cancer diagnosis. However, the pilot nature of this study and small sample size meant that the efficacy of the intervention compared with a control condition could not be established.

In summary, the four studies published to date provide preliminary evidence of the feasibility of iCBT interventions for delivering psychosocial interventions for coping with cancer. However, studies examining the efficacy of iCBT programs aimed at heterogeneous cancer types have so far been limited by either (1) small sample sizes and consequent lack of power, (2) lack of a control condition, and/or (3) not providing analysis of the longer-term impact of the intervention. Further, only our group have investigated a self-guided intervention that is (a) independent of discussion board components and therefore truly self-guided and (b) applicable to delivery soon after diagnosis, as opposed to post cancer treatment, and therefore consistent with CBT literature suggesting that treatment for distress at the time of cancer diagnosis is more effective than treatment for distress after treatment for cancer.

This paper reports on the protocol for the proposed RCT to examine the effectiveness of the iCBT intervention in a multisite setting.

### Aims and hypotheses

This study aims to evaluate the efficacy of the next iteration of our self-help internet cancer coping intervention (‘*Finding My Way’*) in improving wellbeing and quality of life of early-stage cancer patients over time, using a multi-site RCT.

A secondary aim is to investigate moderators of therapeutic change, consistent with recommendations that RCTs should identify who benefits most, and under what conditions, from psychosocial interventions [30]. For the present study, factors that have been previously shown to predict distress will be examined for their potential to moderate the effects of the intervention; namely, availability of social support, cognitive vulnerability to distress, and motivation to seek information [8,31].

Therefore it is hypothesised that:Intervention participants will report greater improvements compared to attention-control participants in the primary outcome, distress, from baseline to post-treatment and 3- and 6-month follow-up;Intervention participants will report greater improvements compared to attention-control participants in the secondary outcomes coping and HRQOL over time;Primary and secondary outcomes will be moderated such thatThe significant changes over time in distress between groups will be moderated by social support, cognitive vulnerability to distress, and motivation to seek information, andThe significant changes over time in coping and HRQOL between groups will be moderated by social support, cognitive vulnerability to distress, and motivation to seek information.

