#### Secondary outcomes

Secondary outcomes for this study include Health-Related Quality of Life (HRQOL), coping, and the economic impact of the intervention in terms of Health Service Utilisation. HRQOL is measured using the European Organisation for Research and Treatment of Cancer Quality of Life Core Questionnaire [35], a 30-item comprehensive health related quality of life assessment for cancer patients which yields a global QOL score, and five functional subscales (physical, emotional, social, role, cognitive).

Coping is measured with the mini-Mental Adjustment to Cancer Scale (mini-MAC: [36]), a 29-item scale yielding 5 factors: Fighting Spirit, Helplessness/Hopelessness, Anxious Preoccupation, Fatalism, and Cognitive Avoidance. Items are responded to on a 4-point scale ranging from ‘*definitely does not apply’* to ‘*definitely does apply*’.

Health Service Utilisation is examined using the 17-item Health Service Utilisation Questionnaire [37], which assesses health service use in the previous 12 months in terms of whether patients have been hospitalised and the number of visits to doctors and other health professionals. Hospitalisation is indicated as *no*/*yes day only*/*yes spent at least one night* (with number of days then recorded). Visits to GPs/hospital doctors/specialist doctors are indicated on a 7-point scale ranging from *none* to *25 or more times*, and utilisation of other health professionals (e.g. physiotherapist) is indicated as *yes* or *no*.

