### Analysis

#### Sample size

Longitudinal sample size calculation for repeated measures was conducted using a program developed by Hedeker [42]. Previous online interventions targeting distress in community samples have effect sizes ranging from .42 to .65 for depression, and from .29 to 1.74 for anxiety [19]. Therefore, a conservative small-to-moderate effect size was selected for the current study. Based on the pilot RCT findings, an attrition rate of 21% at each of the assessment points can be expected [29]. Thus for a study with 2 groups and 4 assessment points, power set at 0.80, statistical significance set at α = .05 (two tailed), total attrition set at 21%, an effect size set at 0.35 SD, and an expected primary endpoint standard deviation of 4.0 at each time point [43], 94 participants per group are required, summing to a total sample of 188 participants.

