#### Statistical analysis

Quantitative data will be analysed using the Statistical Package for the Social Sciences (SPSS) Version 17.0. Baseline differences between groups will be investigated using t-tests for continuous measures and *χ*^2^ tests of independence for categorical measures. Linear Mixed Effects Models (LMEM) will be employed to examine the efficacy of the intervention. The LMEM calculates a regression line for each individual while controlling for baseline observation (fixed main effects). Baseline observations will be entered as covariates to eliminate the influence of baseline variability, resulting in a 2 (group: intervention; control) X 3 (time: post-program; 3-month follow-up; 6 month follow-up) fixed effects model for each outcome variable, with random effects accounting for individual variation. This approach effectively equalises conditions at baseline and consequently allows for direct comparison between conditions at each follow-up point. In this context, (a) interactions between condition and time, (b) main effects of group and (c) post-hoc pairwise comparisons at each follow-up point are all indicators of intervention effects. This analysis offers the benefit of estimation maximisation; it provides joint modelling for each participant of observed and missing data based on maximising likelihood for population parameters as a function of the observed data. LMEM analyses are therefore robust with respect to handling missing data and unbalanced designs in longitudinal research as all participants with at least one observed *post-treatment* data point are included. That is, as baseline data is entered as a covariate, participants who do not complete any of the post-program assessments are not retained. To overcome this limitation and ensure this trial adopts a fully intention-to-treat design, multiple imputation will be performed for participants with only baseline-data. Therefore all participants, regardless of missing data at one or more assessment points, will be included in analyses and accurate parameter estimates obtained. Within-group effect sizes and reliable change indices will be calculated to provide a measure of the magnitude and clinical significance of changes respectively. To test for moderation, separate LMEM analyses will be conducted for each combination of moderator and outcome variable, where the moderator and group are entered in model 1 to control for main effects. The product term is then entered in model 2, to represent the interaction between group and moderating variable, and will indicate the moderating effect.

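### Hypothesis 2 has no single decision rule: 11 coping and HRQOL scales, each with five possible indicators of effect, could be read as support

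*Protocol article*

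**What the plan says.** - **Hypothesis (Aims and hypotheses).** Hypothesis 2 is directional: "Intervention participants will report greater improvements compared to attention-control participants in the secondary outcomes coping and HRQOL over time". It names two domains and no scale. The abstract's aim also lists both domains next to distress: "in improving distress, coping and quality of life for individuals with a recent diagnosis of early stage cancer of any type".
- **Coping (Secondary outcomes).** The mini-MAC is "a 29-item scale yielding 5 factors: Fighting Spirit, Helplessness/Hopelessness, Anxious Preoccupation, Fatalism, and Cognitive Avoidance". No total score is mentioned.
- **HRQOL (Secondary outcomes).** The questionnaire is one "which yields a global QOL score, and five functional subscales (physical, emotional, social, role, cognitive").
- **Analysis (Statistical analysis).** A separate model, two groups by three follow-ups with baseline as covariate, is fitted for each outcome variable. The group-by-time interaction, the group main effect and the "post-hoc pairwise comparisons at each follow-up point are all indicators of intervention effects".
- **Significance level (Sample size).** The only level in the article is "statistical significance set at α = .05 (two tailed"), within the calculation for the primary endpoint. No level is given for the secondary outcomes.

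Distress is clearly labelled primary, and coping and HRQOL secondary, in the abstract's methods paragraph and in the Outcomes section.

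**The concern.** A reader who wants to know whether Hypothesis 2 was supported has no defined test to look at. There are 11 scales, and on each of them five results could be cited: one interaction, one main effect and three pairwise comparisons. That is 11 × 5 = 55 results for one hypothesis. The analysis section puts these indicators on the same footing and does not say which decides.

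At stake is a statement that the program improves coping or quality of life when it rests on one subscale, or one subscale at one time point, that crossed the threshold by chance. The moderation hypotheses add weight, because they take significant between-group changes in coping and HRQOL as their starting point.

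**Working it through.** **The plan's own figure.** The article gives no error rate for the secondary outcomes, so there is none to reproduce. Its 94 per group concerns the primary endpoint and is not affected by this point.

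**Inputs from the article.** Scales: 5 + (1 + 5) = 11. Indicators per scale: 1 interaction + 1 main effect + 3 pairwise = 5.

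**Assumed inputs.** Two-sided .05 for each test (carried over from the sample-size paragraph); equal correlation r between scales of 0, 0.3, 0.5 or 0.7; correlation c between follow-ups of 0.5 or 0.7; large-sample normal tests; no true effect on any scale. The article gives none of the correlations.

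**Step 1: main effect only, independent scales.**
- At least one false positive in either direction: 1 − 0.95^11 = 0.431.
- At least one in the favourable direction, which is what Hypothesis 2 predicts: 1 − 0.975^11 = 0.243.

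**Step 2: all five indicators on one scale.** Let Z1, Z2, Z3 be the z-statistics at the three follow-ups.
- Pairwise: |Zt| > 1.96 for any t.
- Main effect: |mean(Z)| / √((1 + 2c)/3) > 1.96.
- Interaction: Σ(Zt − mean(Z))² / (1 − c) above the 95% point of chi-squared on 2 df, 5.99.

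Main effect and interaction alone give about 1 − 0.95² = 0.0975. Adding the three pairwise tests, simulation gives 14.5% (c = 0.7) to 15.6% (c = 0.5) per scale, in either direction.

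**Step 3: all 11 scales, by simulation.** Chance of at least one false result; ranges run over c = 0.7 to 0.5.

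| r between scales | Favourable, main effect only | Favourable, main effect or pairwise | Either direction, any of five indicators |
|---|---|---|---|
| 0 | 24% | 46–52% | 82–85% |
| 0.3 | 19% | 36–41% | 76–78% |
| 0.5 | 15% | 29–33% | 65–68% |
| 0.7 | 11% | 22–25% | 52–54% |

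The third column is the one that answers Hypothesis 2 under the rule as written. The last column includes scales on which the intervention looks worse, and an interaction test that has no direction.

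**Step 4: average number of falsely favourable scales.** The favourable rate per scale (main effect or pairwise) is about 5.5 to 6.5%, so 11 × 0.055 to 11 × 0.065 ≈ 0.6 to 0.7 scales per null trial. The count in either direction over all five indicators is 11 × 0.145 to 11 × 0.156 ≈ 1.6 to 1.7.

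**Step 5: after the fix.** With two lead scales and one main effect each, the chance of at least one favourable false result is at most about 1 − 0.975² = 0.049.

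**The case against.** The strongest reply is that this is a condensed journal article. Multiplicity for secondary outcomes, and the ranking of subscales within an instrument, are commonly left to a statistical analysis plan, which is not shown. That stands: the missing adjustment is not in itself an error. What remains is that the article does not simply stay silent. It states that several results per outcome all indicate an effect, and it attaches a directional hypothesis to domains that consist of 11 scales.

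Several stronger readings are tempting, and the document does not support them:

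- *That the plan tests every scale at .05.* The level appears only in the primary sample-size paragraph. Its use elsewhere is an inference.
- *That a chance improvement is likely, at 65 to 68%.* That figure counts errors in both directions. Hypothesis 2 predicts improvement, and the matching figure is 29 to 33% at correlation 0.5. About 50% is reached only with independent scales, which is implausible for subscales of the same questionnaire. For the same reason, 1.6 to 1.7 is not the number of falsely improved scales.
- *That the trial promises to establish benefit on coping and HRQOL.* The Discussion says only that the trial will allow efficacy on them to be examined.
- *That one subscale may carry an efficacy claim after a null primary result.* Nothing in the article says so, and the primary and secondary labels are clear. The article does not rule it out either.

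It is also fair to say that the sentence on indicators applies to the primary outcome too, and that tidying it would remove part of the inflation here. The 11 scales without a lead would remain, with about 15% for a favourable main effect at correlation 0.5.

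**Conclusion.** The point holds in a limited form. Read together, Aims and hypotheses, Secondary outcomes and Statistical analysis leave Hypothesis 2 without a defined test, and the rule that is written down is permissive. On the assumptions listed, the chance of at least one favourable false result is about 29 to 33% at between-scale correlation 0.5 (22 to 25% at 0.7, 46 to 52% at 0). With the main effect alone it is about 15% (11% and 24%). One two-sided test at .05 has 2.5% in the favourable direction, so the inflation is roughly 12- to 13-fold under the full rule (29/2.5 to 33/2.5) and 6-fold with the main effect alone (15/2.5), both at correlation 0.5.

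The size depends on the assumed .05 per test, equal correlations and reading any one indicator as sufficient. The primary outcome and its sample size are not touched.

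**What to change.** In Statistical analysis, or in the analysis plan before unblinding:

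1. Define one contrast for each secondary scale: the group main effect over the three follow-ups.
2. Name one lead scale per domain for Hypothesis 2: the global QOL score for HRQOL, and one mini-MAC factor for coping, chosen by the sponsor.
3. Report the other four mini-MAC factors, the five functional subscales, the interactions and the pairwise comparisons as exploratory, with estimates and confidence intervals.

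Alternatively, label all 11 scales exploratory and reword Hypothesis 2 to match.

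Making the secondary tests conditional on the primary result, or a Holm adjustment, is optional. Bonferroni over all 11 scales would be costly: at .05/11 = .0045, a scale with 80% power at .05 would fall to about 49%.

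The cost is a few sentences, with no new data or patients. The small downside is that an isolated significant subscale or time point can no longer be claimed as efficacy.
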